## Abstract

Considerable fundamental studies have focused on the mechanisms governing cognitive flexibility and the associated costs of switching between tasks. Task-switching costs refer to the phenomenon that reaction times and accuracy decrease briefly following the switch from one task to another. However, cognitive flexibility also impacts day-to-day life in many complex work environments where operators have to perform several different tasks. One major difference between typical tasks examined in fundamental studies and real-world applications is that fundamental studies often rely on much more similar tasks, which is not the case for real-world applications. In the latter, operators may switch between vastly dissimilar tasks. Therefore, this behavioural study aims to test if task-switching costs are different for switches between similar and dissimilar tasks. The proposed protocol has participants switch between 2 pairs of two tasks each. Between pairs, there is more dissimilarity, while the two tasks within each pair are more similar. In addition, this study examines the impact of mental fatigue and interference in form of confounding information on cognitive flexibility. To induce mental fatigue the participants’ breaks between blocks will be limited. We expect that dissimilarity between tasks will result in greater task-switching costs.

## 1. Introduction

Cognitive Flexibility, the ability to adapt our behavior and thoughts to the environment, is one of the most important aspects of human cognition [1]. A classical paradigm to study cognitive flexibility is the task-switching paradigm [2–7]. This paradigm requires the participant to switch between two or more relatively simple tasks continuously. Results consistently show that switching between tasks results in task-switching costs (TSC) in the form of increased reaction times and error likelihood following a switch [2–7].

The existence of TSC poses the question of how these effects occur. Two main theories explain this behavioral phenomenon. The Inference view and the Reconfiguration view [8,9]. First proposed by Allport in 1994 the inference view states that during a switch trial the previously activated task set, that is the components relevant to the task (Monsell & Mizon, 2006) [13], interfere with the newly activated task set; The Reconfiguration view [9]on the other hand proposes that task set parameters need to be activated or retrieved from long term memory when a task switch occurs.

In the pursuit of validating one or the other theories, a multitude of variables, such as preparation time, previous interference residual switch costs, working memory, bivalence, similarity and other factors, have been investigated with regard to their relation to TSC [4,10–13]. For a review of the two opposing theories and a summary of the influences of factors on TSC see [11,14].

The similarity factor is of interest for research on cognitive flexibility, especially as most fundamental research has only focused on very similar tasks [7,15]. In these designs, ecological validity is not always given, as task switching in reality may occur between vastly dissimilar tasks. Ecological validity is important with regard to cognitive flexibility, as research has shown that issues with cognitive flexibility have major real-world implications, especially in the domain of Human-Machine Interaction (HMI; [16–20]).

If the fundamental research conducted on cognitive flexibility is to be applied to real-world contexts and problems, the question arises as to what extent these fundamental findings also apply to a realistic context. If this is not the case then it is of interest to see the differences between task-switching in a fundamental context and task-switching in an ecologically valid context [21–23].

This question makes similarity between tasks a critical aspect of understanding cognitive flexibility, as it could be argued that classical task-switching paradigms involve tasks [1] that are more similar than task-switching that is required of operators in complex operations [18].

Some studies have investigated the effects of similarity and closely related effects on task-switching [2,21–24]. In study [2], participants were presented with rectangles of different shapes and colors. Participants had to switch between two sets of two similar tasks and make binary decisions. The tasks were judgements of height, width, hue and intensity. The assumption, which was later validated, was that the width and height, as well as hue and intensity tasks, were more similar.

The responses within that study were univalent (each response possibility, for each task, was mapped onto a different key on the keyboard, or a different vocal response). However, the stimuli were bivalent, meaning that each stimulus could be applied to all tasks. Bivalency is of interest, especially when looking at task-rule incongruent and task-rule congruent responses [11]. In studies where both the stimuli as well as the responses are bivalent (the same responses are used for all keys, and all stimuli can be applied to all tasks), task-rule congruent stimuli (stimuli for which the correct response to the relevant as well as the irrelevant task are the same) are typically faster than task-rule incongruent stimuli (stimuli for which the correct response to the relevant task is not the same as to the irrelevant task [10]. This does not directly apply to the study of [15], as here each response was mapped to a different key and therefore the effect of task-rule incongruency was kept constant. The recent study [21], made use of a similar dimensional design of different tasks. In addition to switching between two tasks, the switch rules could also be different. The work of (Kleinsorge & Heuer, 1999) [23], also uses a dimensional design but here instead of similarity, compatibility of the stimuli is added as a second factor. Further expanding on this is the 2004 study by Kleinsorge [22]. Using a factorial design, participants have to switch between a parity or numerical magnitude task, while either focusing on the numeric value or the number of digits displayed. Participants of this study had to therefore switch between 4 different tasks, however except for switches between tasks where both factors were changed, the tasks all had one factor in common (either the actual task instruction or the part of the stimulus on which to focus).

Several questions arise here: are the incongruency effects that arise in studies using a bivalent design (when the task-relevant cue indicates answer A and the task-irrelevant cue indicates answer B) additive? That is to say, in a task-switching design using 4 different tasks, is there a difference between 1 irrelevant cue biasing towards the incorrect answer or 3 irrelevant cues biasing towards the incorrect answer? What has a stronger impact on TSC, similarity or bivalence/congruency? Does it matter if the biasing cue from a different task comes from a more similar or a more dissimilar task?

Beyond exploring these questions that have a very fundamental ft in understanding cognitive flexibility, there is also an interest when going back to more ecological concerns. Task-Switching in an ecological context may involve switching between tasks where similarity and bivalence are independent of each other. The here proposed study is also lacking in ecological validity. However, investigating the mechanisms of cognitive flexibility in the context of more or less dissimilar tasks, may facilitate future research to experiment with vastly dissimilar tasks that better resemble the real world.

With the goal of paying attention to factors vital to ecological validity mental fatigue and time on task (TOT) were identified as important covariates. While studies with a multitude of different tasks often show an increase in reaction time and a decrease in accuracy as TOT [25–27], studies on cognitive flexibility, show that the increase in TSC is significantly bigger, than the overall increase in reaction time and decrease in accuracy [28–31]. Furthermore, mental fatigue has been identified as a risk factor in several types of complex operations, that simultaneously requires the operator to maintain a degree of cognitive flexibility [20,32–34] Beyond complex operations, deficits in cognitive flexibility are also associated with several psychiatric/ psychological conditions. Research has shown deficits in cognitive flexibility associated with Parkinson’s disease, Schizophrenia, attention deficit/Hyperactivity Disorder (ADHD) and Depression [35,36] The results of this study may also help understand the impact the pathologies have on the lives of those affected, in the context of cognitive flexibility.

NOTE: For the remainder of this preregister we will no longer use the term bivalency to explain, but rather the terms conflict and congruency. This is because in the experimental design 4 different levels of conflict are planned. These consist of a level where only the task-relevant cue is present and three conditions were also other task-irrelevant cues are present. However, it was decided that the task’s irrelevant cues are always incongruent. This decision was made to allow the evaluation of accuracy in addition to reaction time as a dependent variable. If we were to involve trials where a task-irrelevant cue indicates the same correct answer as the task-relevant cue, it would be impossible to know if the participant, given that he responds correctly, if this correct response was also based on the correct cue or the task-irrelevant cue.

## 2. Hypotheses (required)

2.1. Task switching cost
2.1.1. Following a switch of the task, the reaction time on said trial is higher than the average reaction time on trials of the same task where previously no switch occurred.2.1.2. Following a switch of the task, accuracy on said trial is lower than the average accuracy on trials of the same task where previously no switch occurred.2.2. Similarity Effects: Task Switching costs (hypothesis 1; Reaction time and accuracy), are more pronounced if the switch is between two more dissimilar tasks.2.3. Conflict Effects:
2.3.1. An incongruent stimulus will result in a higher reaction time regardless of whether the trial is a switch trial or a repetition trial.2.3.2. An incongruent stimulus will result in a lower accuracy regardless of whether the trial is a switch trial or a repetition trial.2.4. Mental Fatigue:
2.4.1. As time on task increases, the reaction times will increase regardless of whether the trials are switch trials or repetition trials.2.4.2. As time on task increases, error likelihood will increase regardless of whether the trials are switch trials or repetition trials.2.4.3. As time on task increases, Task Switching costs (hypothesis 1) will increase

Design Plan

## 3. Study type: Experiment

    

## 4. Ethics statement

Ethical Consent was obtained from the Comité d’Éthique de la Recherche—CER at the Université Fédérale Toulouse Midi-Pyrénées Approval for written consent was obtained on June 2. 2020 (ID 2022–521).

## 5. Blinding

Within subjects design. Every participant will complete the same trials as all the other participants.

Participants will be aware, that the goal of the experiment is to study cognitive flexibility and that mental fatigue plays a role. Participants will not be made aware of the hypotheses to avoid demand characteristics.

Personnel interacting with the data and the participants are aware of the goal as well as the experimental design of the study (necessary for the data analysis).

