**Fig 2 pone.0279021.g002:**
[figure not shown]
Larger example of stimuli with cue relevant for Task 3.

During the task, participants have to perform consecutive trials, where the task and stimuli will change quasi-independently from trial to trial.

For each trial, participants are presented with 3 quasi-independent pieces of information. They are presented with an instruction for the current trial in form of the task name (eg. VERTICAL/HORIZONTAL, presented 300ms before the actual stimulus) and two stimuli in form of signs or numbers. Based on the stimuli and the instruction participants are instructed to then respond as fast as possible, using either the S or the L key on a keyboard (keys were selected as they are located at a comfortable distance on the keyboard, in order to avoid straining the hands of the participants, keys will be marked with stickers for participant ease).

In total there are 96 different conditions for each trial (4 Tasks * 3 Switching conditions * 4 Congruency Conditions * 2 Response types). However, as differences in performance of individual tasks, as well as response type, are not hypothesized to have any impact on the performance of participants, 12 main conditions remain.

*Task-Switching Conditions*:

Each trial (n) is classified into one of the three Task-Switching Conditions depending on the task in trial n-1. If the task remains the same, the trial is a repeat trial. If the task switches, but remains within the same domain (LOW/HIGH to EVEN/ODD or VERTICAL/HORIZONTAL to COLD/HOT and vice versa), it is considered an internal switch trial. Finally, switches from one domain into the other (LOW/HIGH or EVEN/ODD to either VERTICAL/HORIZONTAL or COLD/HOT and vice versa) are considered external switch trials.

Note that patterns in Task 3 are not clearly visible in the document, please refer to Fig 2.

*Congruency Conditions*:

Depending on the stimuli that are presented a trial may evoke different degrees of conflict as to the correct response required. This occurs when the **task-relevant information of the stimulus** indicates, that eg. response 1 is correct, while in the presence of a non-relevant cue biasing the response in the incorrect condition. Here 4 different conditions exist.

In the no-conflict condition, a stimulus only presents one piece of information, the relevant one. In Fig 3 the stimuli in the no-conflict condition provide no information relevant to each of the remaining 3 tasks.

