**Fig 3 pone.0279021.g003:**
[figure not shown]
Examples of the different congruency conditions.

The internal conflict condition adds a piece of information that would indicate the opposite response in the other task of the same domain. In the example, the 3 is the relevant number, due to its position, as the participant is indicated to perform the Even/ Odd task (which is always based on the second number), but the other stimulus (, the 2) would require the participant to respond with the other response if the task were the Low/High task (the task for which, the first number is relevant).

The external conflict condition is similar, with the only difference being, that the non-relevant task is not from the same domain, but is one (and always only one) of the tasks from the other domain.

The final condition, internal & external conflict combines the two other conflict conditions, where both the other internal task and one (and always only one) of the external task, bias the participant towards an incorrect response.

In order to avoid participants using task-irrelevant cues as a strategy to increase performance (Logan & Zbrodoff, 1979) half of the trials will include congruent task-irrelevant stimuli and half of the trials will include task-irrelevant incongruent stimuli. Task irrelevant stimuli will always all be either congruent or incongruent. The downside of this is, that it becomes impossible, during trials with congruent task-irrelevant stimuli, to determine whether a correct or incorrect answer occurred due to the task-relevant or task-irrelevant stimulus. For any analysis that requires this, only the incongruent task-relevant trials may be used.

The locations of the relevant stimuli for the numeric tasks were chosen to be Low/High on the left and Even/Odd on the right for the following reason. Should participants perceive two single digits not as e.g. seven and one but as seventy-one, this would not change the responses. As the Even/Odd relevant number is located (right, or for this discussion 2.) it determines whether a number is odd or even, independent from the number to the left of it (that is to say, both 1 and 71 are odd numbers). In a similar way, the size of the first number is somewhat independent of the second number (7 is larger than 5, but 71 is also larger than any number in the fifties).

Trial Setup:

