## 8. Randomization

Participants are not randomized (within-subjects design), however, the trials that participants will complete are quasi-random. That is to say, trials will appear in a random order, which ensures a balanced design and equal probabilities of each trial occurring.

Sampling Plan

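### One relative category-to-key mapping appears to apply to every participant, so task-pair compatibility may enter the similarity contrast (hypothesis 2.2) as an unremovable constant of unknown sign

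*Protocol article*

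**What the plan says.** Section 7 (Study design) has participants answer each trial "using either the S or the L key on a keyboard", whichever of the four tasks is cued. The article does not say which category goes to which key.

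Section 5 (Blinding) says "Every participant will complete the same trials as all the other participants". Section 8 adds: "Participants are not randomized (within-subjects design), however, the trials that participants will complete are quasi-random". The design count in section 7 reads "In total there are 96 different conditions for each trial (4 Tasks * 3 Switching conditions * 4 Congruency Conditions * 2 Response types", with no key-mapping factor, and section 12 (Manipulated variables) lists none. When that count is reduced to 12 main conditions, individual tasks, "as well as response type, are not hypothesized to have any impact on the performance of participants".

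The worked example of internal conflict has a 3 judged as even or odd beside a 2 that "would require the participant to respond with the other response if the task were the Low/High task". In that example low and odd are on opposite keys, so low shares a key with even.

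The switch types are defined by domain: "LOW/HIGH to EVEN/ODD or VERTICAL/HORIZONTAL to COLD/HOT and vice versa), it is considered an internal switch trial", while "LOW/HIGH or EVEN/ODD to either VERTICAL/HORIZONTAL or COLD/HOT and vice versa) are considered external switch trials". Hypothesis 2.2 predicts larger switch costs for the external type. The Analysis Plan adjusts for participant and task with dummy variables and names no term for the pair of tasks involved in a switch.

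**The concern.** With two keys and four binary tasks, any two tasks can be paired in two ways: the first categories share a key, or they are on opposite keys. The choice matters twice. It decides which displays count as congruent, and it may make moving between two tasks easier or harder if the categories on one key belong together in everyday use. Low with cold and high with hot is the obvious candidate.

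If all participants have the same relative mapping, each of the six task pairs is in one of its two states for everyone. Any effect of that state is then part of the external or internal mean, and the comparison in hypothesis 2.2 cannot separate it from task similarity. Random trial order does not help, because the effect belongs to the pair of tasks and not to the order.

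**Working it through.** **Inputs from the article.** Four tasks in two domains, three switch types, four conflict levels, two response types; 5 blocks of 336 trials; 30 participants planned.

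**The plan's own count.** 4 × 3 × 4 × 2 = 96 conditions, and 3 × 4 = 12 main conditions. Both reproduce. Key mapping is in neither.

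**Does the text imply one mapping?** Congruency of a display depends on the relative mapping: reversing the keys of one task turns a congruent display into an incongruent one. If everyone sees the same trials with the same congruency labels, everyone has the same relative mapping. Exchanging S and L for all tasks together would not change this.

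**Weights.** Directed transitions:
- external: 4 tasks × 2 tasks of the other domain = 8, two for each of four pairs, so 2/8 = 0.25 per pair;
- internal: 4 tasks × 1 task of the same domain = 4, two for each of two pairs, so 2/4 = 0.5 per pair.

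With equal frequencies (assumed), 5 × 336 = 1680 trials give 1680/3 = 560 per switch type. That is 560 × 0.25 = 140 per external pair and 560 × 0.5 = 280 per internal pair, for each participant.

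**Shift in the contrast.** Let c be the mapping-specific effect on RT for a pair:

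shift = 0.25 × (sum of c over four external pairs) − 0.5 × (sum of c over two internal pairs).

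The article gives no value of c, so these are illustrations:
- only LOW/HIGH–COLD/HOT, c = 20, 40 or 80 ms: 0.25c = 5, 10 or 20 ms; c = −40 ms: −10 ms;
- that pair at 40 ms and one internal pair at +20 ms: 10 − 10 = 0 ms;
- the same with the internal pair at −20 ms: 10 + 10 = 20 ms.

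**Simulation.** Task dummies fitted, no true similarity effect, trial SD 150 ms (assumed), c on LOW/HIGH–COLD/HOT only, 15 replicates (6 at N = 90):

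| Mapping | N | c (ms) | Mean bias (ms) |
|---|---|---|---|
| fixed | 30 | 20 | 4.4 |
| fixed | 30 | 40 | 9.7 |
| fixed | 30 | 80 | 20.6 |
| fixed | 30 | −40 | −10.2 |
| fixed | 90 | 40 | 10.2 |
| half aligned, half crossed | 30 | 40 | 0.2 |

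The biases agree with 0.25c up to simulation error. Task dummies do not remove them, and tripling N does not shrink them.

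**Scale.** With an assumed residual SD of 300 ms, the standard error of the contrast from trial noise is 300 × √(2/(560 × 30)) = 3.3 ms. With an assumed between-participant slope SD of 30 ms it is √(3.27² + 30²/30) = 6.4 ms. A shift of 5 to 10 ms is then 5/6.4 = 0.8 to 10/6.4 = 1.6 standard errors.

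**The case against.** The strongest objection is that no sentence states a single mapping. The sentence in section 5 explains a within-subjects design and is not about keys. Section 8 contrasts participants with trial order, and the conflict example is one example. The article links to a fuller protocol, and the figures are not reproduced in the text at hand. Counterbalancing could be described there. This stands: one mapping is the natural reading, not a certain one, and the first request must be to state it.

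Several stronger readings are tempting but not supported:
- **That the constant loads only the dissimilar side.** This is true of LOW/HIGH–COLD/HOT alone. A fixed mapping also fixes LOW/HIGH–EVEN/ODD and COLD/HOT–VERTICAL/HORIZONTAL, which are internal and carry twice the weight per pair.
- **That the bias favours the hypothesis.** If the order of words in the task names sets the keys, as the low-with-even example would allow, low shares a key with cold. That might ease some external switches and work against hypothesis 2.2. The article does not confirm the rule.
- **That hypothesis 2.3 is biased in the same way.** It concerns incongruent against congruent stimuli overall, with no separate hypothesis for external conflict.
- **That Response enters the RT model only as a main effect.** The Analysis Plan lists variables, not terms, and Table 1 tests interactions that the list does not show.
- **That the left and right positions of the digits are an unexplained fixed choice.** Section 7 gives a reason for them.

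**Conclusion.** The point holds as a cheap improvement to the design, with low confidence about its practical effect. If the mapping is fixed, compatibility between categories sharing a key is a constant in the external-minus-internal contrast, with the weights shown. Neither the planned covariates nor sample size removes it. The weights assume equal transition frequencies within each switch type, in line with the balanced design of section 8. All millisecond values and SDs are assumptions, and no net size or sign can be given. The article does not show that the test of hypothesis 2.2 is biased, only that its description does not protect the test from this source.

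**What to change.** 1. **State the category-to-key mapping** for all four tasks, and whether it varies between participants.
2. **If it is fixed, counterbalance it with four assignments.** Keep LOW/HIGH as the reference, reverse EVEN/ODD and COLD/HOT independently, and reverse VERTICAL/HORIZONTAL when exactly one of those two is reversed:

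| Assignment | EVEN/ODD | COLD/HOT | VERTICAL/HORIZONTAL |
|---|---|---|---|
| A | as is | as is | as is |
| B | reversed | as is | reversed |
| C | as is | reversed | reversed |
| D | reversed | reversed | as is |

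Each of the six task pairs is then in each state in two of the four assignments. Reversing only the two visual tasks together would leave both internal pairs fixed.

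3. **Recompute congruency for each assignment**, and match key stickers and instructions to it.
4. **Include assignment and assignment × trial type in both models**, coded so that the trial-type contrast averages equally over assignments. If participants enter as dummies, as planned, these absorb the assignment main effect; the interaction remains estimable and is the term that matters here.
5. **If data collection has begun**, report a sensitivity analysis of hypothesis 2.2 by task pair, or without LOW/HIGH–COLD/HOT transitions. This shows whether the result depends on particular pairs but does not replace counterbalancing.

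The cost is a lookup table in the task script, alternative stickers and instruction texts, and some added between-participant variance. Since 30/4 = 7.5, there would be 7 or 8 participants per assignment, so the interaction would be estimated imprecisely. No extra participants or trials are needed.
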